## Method

### Study design

The feasibility study will employ a pretest posttest observational design using mixed methods to evaluate acceptability, demand, implementation and practicality [34] of the Responsive CARE intervention. Using a mixed methods approach will allow for the collection of quantitative data in terms of the demand for the intervention as well as rich qualitative data to understand the factors affecting implementation that may ultimately impact on the intervention’s sustainability and/or scalability. Purposive sampling will be used for the qualitative study components. Interviews will cover five main areas: understanding of trauma-informed care practice, experience of trauma-informed care, clinician’s readiness to change, acceptability of the Responsive CARE intervention and identify potential barriers and enablers to implementing an e-learning package within organizational culture.

A mixed method, pretest posttest comparison design will be used to examine preliminary effectiveness, with consecutive sampling of children and caregivers. Baseline quantitative data will be collected during a 3-month control period followed by a 3-month intervention period. Follow-up of participants will be completed at 3 months and 6 months after baseline for participants in the control and intervention periods. Between the control and intervention periods, there will be a 1-month period to implement the e-learning intervention. Qualitative interview data will also be collected from caregivers in the control and intervention periods, who will be purposively sampled.

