(4) Intervention details: time taken to complete the intervention, number of times accessed and number of staff who complete the package per discipline

These other outcomes will be used to describe the control and intervention groups and use of the intervention, as well as to be entered into analyses as predictors or confounding factors to be controlled for.

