#### Patient-centred outcomes

Sociodemographic, clinical and intervention data will be summarised using descriptive statistics (e.g. mean and standard deviation and 95% confidence intervals) and presented for each group separately. Potential confounding variables for the outcomes are considered a priori to be the following: days to re-epithelialisation, percentage maximum burn depth, days post-burn at baseline, type of injury and number of surgical procedures (e.g. skin grafting) and severity of scarring and child traumatic stress symptoms. Potential confounding variables that are identified as significantly different or different to a clinically meaningful extent between the control and intervention group will be controlled for in analyses where appropriate. As this is a feasibility study, the study will likely be underpowered; therefore, quantitative outcomes will be interpreted only as preliminary findings.

Control period participants will be matched with intervention period participants on factors including age, gender, education and total body surface area burned to examine between group differences. Differences in outcomes between the groups will be analysed using generalised linear (mixed) models or equivalent analyses to examine differences at 3-month and 6-months post-procedure or 3-months and 6-months post-burn where applicable, adjusting for the baseline value of the outcomes where appropriate (with terms included for stratification and confounding variables where applicable). A sensitivity analysis will be conducted using imputation techniques to replace non-ignorable data that is considered to be missing at random over the follow-up period, to determine whether bias is likely in the complete case analysis.

Patient-centred outcome data will be stratified by age to coincide with different versions of patient-reported outcome measures for different age groups and caregiver report versus child report.

The mean difference in change scores for health professional’s knowledge and self-efficacy will be calculated for individual questions and analysed using a Wilcoxon paired test (assuming parametric assumptions are not likely to be observable in this relatively small sample).

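### Children are matched at the analysis stage, but no matched-set term is named, and the two statements on adjustment disagree on whether the matching factors enter the model

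*Protocol article*

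**What the plan says.** Study design describes an unmatched enrolment: a "pretest posttest comparison design will be used to examine preliminary effectiveness, with consecutive sampling of children and caregivers". Matching first appears under Data analysis, Patient-centred outcomes: "Control period participants will be matched with intervention period participants on factors including age, gender, education and total body surface area burned".

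The same paragraph gives the model: "Differences in outcomes between the groups will be analysed using generalised linear (mixed) models or equivalent analyses". It adjusts for the baseline value where appropriate, "with terms included for stratification and confounding variables where applicable". No pair or matched-set term is mentioned.

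The preceding paragraph lists the confounders: "Potential confounding variables for the outcomes are considered a priori to be the following: days to re-epithelialisation, percentage maximum burn depth, days post-burn at baseline". The list goes on to injury type, surgical procedures, scarring and traumatic stress symptoms. None of the four named matching factors is on it. The rule for using the list is conditional: "Potential confounding variables that are identified as significantly different or different to a clinically meaningful extent between the control and intervention group will be controlled".

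Two other statements bear on this. Age is handled at least coarsely: "Patient-centred outcome data will be stratified by age to coincide with different versions of patient-reported outcome measures". And the section Primary health professional outcomes, after listing registry and self-report data that include TBSA, age, gender and household education, closes by saying these are "to be entered into analyses as predictors or confounding factors to be controlled for". That sentence has no imbalance condition.

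**The concern.** Matching on prognostic factors makes the outcomes of matched children correlated. The analysis has to reflect this, through a matched-set term or by including the matching factors. Otherwise the standard error of the between-period difference does not describe the estimate's true variability.

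The stated adjustment rule works against this. It brings a variable in when the groups differ on it, and matching is meant to make the groups agree on TBSA, gender, education and age. The better the matching works, the less likely the rule is to bring these factors in. The other section points the opposite way, so an analyst could follow either instruction and claim to have followed the plan.

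At stake are the confidence intervals for pain, itch and distress. The plan already expects low power and treats these results as preliminary, so the intervals are what readers will mainly use. Losing precision that the matching supplies is avoidable.

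**Working it through.** **1. The plan's own figure.** Recruitment (Quantitative study component) anticipates 180 children: 30 per month × 6 months = 180. This reproduces. It is a count of available children, not a power calculation. An equal split implies 180 / 2 = 90 per period, which the article does not state.

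**2. Which matching factors enter the model?**

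| Factor | On the a priori confounder list? | Likely to differ after matching? | Covered by the unconditional statement? | Other route |
|---|---|---|---|---|
| Age | No | No | Yes | Age strata for questionnaire versions |
| Gender | No | No | Yes | None named |
| Education | No | No | Yes | None named |
| TBSA | No | No | Yes | None named |

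The conditional rule tends to leave out gender, education and TBSA, and leaves age only as coarse strata. The unconditional statement puts all four in.

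**3. Size if the model ignores the matching (1:1, without replacement).** Assumptions, none given in the article: m = 90 complete pairs, SD = 1, two-sided 5%, normal approximation, a difference of 0.4 SD, and within-pair correlation ρ remaining after other adjustment.

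- Unpaired: SE_u = √(2/m) = √(2/90) = 0.149
- Respecting the matching: SE_p = √(2(1−ρ)/m)
- Ratio: SE_u / SE_p = 1/√(1−ρ)
- True size of the unpaired test: 2[1 − Φ(1.96 × SE_u / SE_p)]
- Power, unpaired: Φ((0.4 − 1.96 × SE_u) / SE_p); matched: Φ(0.4 / SE_p − 1.96)

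| ρ | SE_p | SE_u too large by | True size of unpaired test | Power, unpaired / matched |
|---|---|---|---|---|
| 0.05 | 0.145 | 3% | 4.4% | 77.1% / 78.6% |
| 0.1 | 0.141 | 5% | 3.9% | 77.7% / 80.7% |
| 0.2 | 0.133 | 12% | 2.8% | 79.1% / 85.1% |
| 0.3 | 0.125 | 20% | 1.9% | 80.6% / 89.4% |

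For a difference of 0.3 SD, simulation (20,000 data sets per setting, two-sample against paired t test) gave power of 52% against 56% at ρ = 0.1, 52% against 61% at 0.2, and 51% against 66% at 0.3.

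**4. Does adding the matching factors repair it?** This was simulated with 1,500 runs per setting, 90 pairs, and one covariate standing in for the matching factors.

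| Matching | Variance explained | True SD of estimate | Unpaired SE | Paired SE | Covariate-adjusted SE |
|---|---|---|---|---|---|
| Exact 1:1 | 10% | 0.146 | 0.149 | 0.141 | 0.141 |
| Exact 1:1 | 30% | 0.120 | 0.149 | 0.124 | 0.124 |
| Nearest neighbour, with replacement | 10% | 0.182 | 0.147 | 0.140 | 0.140 |
| Nearest neighbour, with replacement | 30% | 0.162 | 0.148 | 0.124 | 0.124 |

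Under exact 1:1 matching, covariate adjustment gives the same SE as pairing, without a pair term. When control children are reused, the direction reverses: the unpaired SE is too small, and simple pairing or covariate adjustment does not cure it. The reuse of the same child has to be reflected in the clustering.

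**The case against.** A reader might infer that the study is matched by design, that the plan prescribes an analysis of two independent samples, and that its standard errors are therefore too wide. The documents do not support that reading, for four reasons.

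- Enrolment is consecutive, and matching is a later analysis step.
- Not naming a matched-set term does not rule one out. A generalised linear mixed model can carry one, and a journal article may leave the random-effects structure to a fuller document.
- The unconditional statement under Primary health professional outcomes covers all four matching factors. The conditional rule says what will be controlled for, not that nothing else may enter. Because the four factors are off the confounder list, it is not certain that the rule governs them.
- The direction of the error depends on matching without replacement and a positive within-pair correlation. The article states neither the ratio nor whether control children can be reused.

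Size can be overstated too. A correlation of 0.5 would make the interval 41% too wide (1/√0.5 = 1.414), but nothing in the article supports that value. Table 2 shows baseline measurements for pain, itch and distress, so baseline adjustment, together with the age strata, would absorb part of the correlation. Under 1:1 matching without replacement the error is conservative, and in a linear model with equal pairs the point estimate is unchanged. No power target or decision rule depends on these tests.

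All of this limits the point without removing it. The two sections still give different adjustment rules, and the more detailed one, followed as written, tends to drop the factors that were matched on. The same section names a paired test for the health professional scores, but nothing comparable for the matched children.

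**Conclusion.** The point holds in limited form. The article matches children on four factors when it analyses them, names no matched-set term, and ties confounder adjustment to observed differences, which tends to exclude what matching has balanced. Another section says the same variables will be entered without that condition. The two must be reconciled.

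The consequence is conditional. With 1:1 matching without replacement and a model that ignores it, the reported standard error is conservative by roughly 5% to 20% for a residual within-pair correlation of 0.1 to 0.3. That range is an assumption, and 90 complete pairs is the most that 180 children could supply. With reuse of control children, the unpaired standard error can instead be too small. Given baseline adjustment, the age strata and the preliminary status of the results, the likely loss is modest. It is worth correcting because the correction costs almost nothing.

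**What to change.** State under Data analysis, Patient-centred outcomes, that every between-period model does one of the following:

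- includes TBSA, age, gender and education as covariates, whether or not they differ between the periods; or
- includes a random effect for the matched set, or uses standard errors clustered on the matched set.

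If matching is with replacement, the clustered standard errors are needed, with a reused child kept in a single cluster. The sentence should therefore say whether control children can be used more than once.

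Exempt the four factors from the rule based on significant or clinically meaningful differences. Reword the closing sentence of Primary health professional outcomes so that both sections give the same rule.

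The cost is a sentence or two of wording. All four variables are already collected. The statistical price is about four degrees of freedom if each factor takes one parameter, and more if education is categorical, out of up to about 180 children.

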**Methods:**

A pre-post, mixed methods design will be employed. Children and caregivers attending hospital for change of burn wound dressings or burn scar management during the 3-month control or 3-month intervention period will be eligible, with follow-up to 6-months post-baseline. All children and caregiver/s will receive “standard care” including burn interventions focused on wound healing, scar management, itch management (both pharmacological and non-pharmacological), counselling, age-appropriate procedural support and burn rehabilitation. Health professional participants will be those involved in the management of children with burns during the study period or their senior managers. Health professional participants who attend a weekly educational clinical meeting will be invited to complete the intervention during a 1-month timeframe between the control and intervention period (or upon their commencement in burn outpatients during the intervention period) using an individualised log-in process. A purposive sample of caregivers and health professionals will be sought for participation in semi-structured interviews. Qualitative data will be analysed using Framework analysis. Feasibility will be evaluated via interviews, digital records of intervention usage and technical assistance logs. The primary outcome measures of effectiveness (pain, itch and distress) will be measured using self-report or behavioural observation. Quantitative data will primarily be analysed descriptively and using generalised linear models.

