### Participants

#### Inclusion criteria

All children and caregivers attending an outpatient service for change of burn wound dressing or burn scar management during the control or intervention period will be eligible to participate. Health professional participants (e.g. medical staff, occupational therapists, nursing staff, social workers, senior managers) will be those involved in the management of children with burns during the study period. Students who are members of the treating burn team for less than 2 weeks during the study will be excluded.

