### Primary patient-centred outcomes

The primary outcome measures of effectiveness to be tested for the main study are pain (self-report or behavioural observation), itch and distress. The Face, Legs, Arms, Cry, Consolability (FLACC) pain scale [39, 40] will be completed by health professionals as a behavioural measure of pain severity. An 11-point numeric rating scale (NRS) will be used by parents and children 8 years or older to rate pain and itch intensity [41]. The NRS is scored from zero to ten, with zero equal to “no pain or itch” and ten equal to “unbearable pain or itch”. Distress will be measured using the Paediatric Emotional Distress Scale—Early Screener [40, 42] for children below 6 years and the Child Traumatic Stress Questionnaire [43] for children aged 7 years and above.

Patient-centred outcome measures to be collected at baseline, 3-months and 6-months post-baseline are summarised in Table 2.

**Table 2 Tab2:** Patient-centred outcome measures and timepoints when administered

Area of focus	Completed by			Outcome measure	Study period (control and intervention)		
	HP	C	YP		Baseline	3-months	6-months
Pain and itch (primary outcome)	X			The Face, Legs, Arms, Cry, Consolability (FLACC) [39, 40]	X	X	
		X	X	Numeric Rating Scale [41]	X	X	
Distress (primary outcome)		X		Pediatric Emotional Distress Scale – Early Screener^a^ [42]	X	X	X
			X	Child Traumatic Stress Questionnaire^b^ [43]	X	X	X
Stress		X		Perceived Stress Scale [44]	X	X	X
Satisfaction with treatment		X	X	Numeric Rating Scale (0 to 10)	X	X	X
Health-related quality of life		X	X	Brisbane Burn Scar Impact Profile [45–47]		X	X
		X	X	EuroQol-5D-Y^c^ [48, 49]	X	X	X
		X	X	CHU-9D^d^ [49, 50]	X	X	X

*HP* health professional, *C* caregiver, *YP* young person aged over 8 years (unless otherwise indicated)

^a^ For children below 6 years

^b^ For children aged 7 years and older ^c^ Administered to caregivers of children 3 years and older  ^d^Administered to caregivers of children 2 years and older

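### Follow-up is scheduled from baseline, but group differences are to be examined at months post-procedure (undefined) or post-burn; one time origin is needed

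*Protocol article*

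**What the plan says.** **Collection.** The Abstract (Methods) describes enrolment in the control or intervention period "with follow-up to 6-months post-baseline". Study design says: "Follow-up of participants will be completed at 3 months and 6 months after baseline for participants in the control and intervention periods". Primary patient-centred outcomes says: "Patient-centred outcome measures to be collected at baseline, 3-months and 6-months post-baseline are summarised in Table 2". All three places count time from baseline.

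**Analysis.** Data analysis, Patient-centred outcomes, says: "Differences in outcomes between the groups will be analysed using generalised linear (mixed) models or equivalent analyses". The stated purpose is "to examine differences at 3-month and 6-months post-procedure or 3-months and 6-months post-burn where applicable". Baseline appears in that sentence only as a value to adjust for, not as the origin from which analysis times are counted.

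**Entry.** Under Inclusion criteria, eligible children are those "attending an outpatient service for change of burn wound dressing or burn scar management during the control or intervention period".

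**Time since burn.** The analysis section lists "days post-burn at baseline" among its a priori potential confounders. It controls for a listed variable only where the two groups turn out to differ on it, either significantly or to a clinically meaningful extent.

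**Times per outcome.** Table 2 marks the FLACC and the pain and itch numeric rating scale at baseline and 3 months, with no mark at 6 months. Both distress measures are marked at all three times.

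**The concern.** Data are collected on one clock and analysed on two others. If the clocks agreed for every child this would be loose wording. They cannot agree for every child, because baseline is whichever eligible clinic visit falls inside the recruitment window. For a child with a fresh burn that visit may be days after the injury; for a scar-management child it may be much later. The article concedes that the interval varies by naming it as a potential confounder.

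Pain, itch and distress plausibly change with time since injury. The design is a non-randomised before-after comparison, so a different mix of early and late attenders in the two periods could look like an effect of the training. The analysis therefore needs a time axis on which every child has scheduled values, and a fixed way of handling stage of recovery. As written, the axis is not the scheduled one, and adjustment for stage of recovery depends on what the data show.

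**Working it through.** The article gives no figure for this interval that could be reproduced. The check sets the sections side by side and adds simple arithmetic.

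**Step 1. Compare time origins.**

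| Section | Times | Counted from |
|---|---|---|
| Abstract, Methods | up to 6 months | baseline |
| Study design | 3 and 6 months | baseline |
| Primary patient-centred outcomes, Table 2 | baseline, 3 and 6 months | baseline |
| Data analysis, Patient-centred outcomes | 3 and 6 months | a procedure, or the burn |

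The qualifier at the end of the analysis sentence can choose between a procedure and the burn. It cannot bring in baseline, which is not offered.

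**Step 2. Post-burn clock.** Let d be the days from burn to baseline. Taking 3 months as 91 days and 6 months as 182 days, measurements fall at d, d + 91 and d + 182 days post-burn. Dividing by 30.4 gives months. The follow-up visits coincide with 3 and 6 months post-burn only when d = 0. The values of d below are **assumptions chosen to show the range**.

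| d (assumed) | Baseline, days post-burn | 3-month visit | 6-month visit |
|---|---|---|---|
| 7 | 7 | 98 days (3.2 months) | 189 days (6.2 months) |
| 30 | 30 | 121 days (4.0 months) | 212 days (7.0 months) |
| 90 | 90 | 181 days (6.0 months) | 272 days (8.9 months) |
| 180 | 180 | 271 days (8.9 months) | 362 days (11.9 months) |

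Three results follow:

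- At small d the mismatch is a few days and harmless.
- At d near 90 the only measurement close to 3 months post-burn is the baseline one. The plan also adjusts for the baseline value where appropriate, so outcome and covariate would be the same number.
- For d above 91 no scheduled measurement falls at 3 months post-burn, since the first is already later. For d above 182 none falls at 6 months post-burn either. This needs no assumption about how d is distributed.

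**Step 3. Post-procedure clock.** The term is not defined. If it means the dressing change or scar visit at which the child enrols, it equals post-baseline and fits the schedule. If it means surgery, it does not fit, and some children may have had none. The preceding paragraph of the same section uses the word for surgery, with skin grafting as its example.

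**Step 4. Times per outcome.** Table 2 schedules two measurements of pain and itch (baseline, 3 months) and three of distress (baseline, 3 and 6 months). Two of the three primary patient outcomes therefore have no 6-month data on the scheduled clock. The analysis sentence speaks of outcomes in general and does not say which are compared at which time.

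**The case against.** **Post-procedure may simply mean the baseline visit.** Children enter at a dressing or scar appointment, and the Abstract mentions procedural support as part of standard care. On that reading this option matches the schedule. It stands as a possible reading, but the article does not state it, and the post-burn alternative remains.

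**Time since burn is not ignored.** It is on the a priori confounder list. That is true, but its use depends on an observed difference between the groups. That is weaker than a fixed term, and it does not repair the time axis.

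**Most children may be enrolled early.** The anticipated 180 children come from an average of 30 new referrals a month over six months (30 × 6 = 180). This gives no support for treating very late enrolment as typical. It does not exclude it either, since scar-management attenders are eligible and a new referral need not be a recent burn.

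**The study is a feasibility study.** The article says it will likely be underpowered and that quantitative results are preliminary. This limits the stakes, but it does not justify analysis times at which no visit is scheduled.

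**Stronger readings that the article does not support.** A reader might infer that the plan commits to a 6-month analysis of pain and itch without data. It does not: the sentence names neither outcome and can be read together with Table 2. A reader might also infer that the clock will be picked after seeing results. Nothing says so, and each child has one set of scheduled measurements whatever the label.

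**Conclusion.** The point holds as a contradiction in time origin. Collection is timed from baseline in three places. The between-group analysis is timed from an undefined procedure or from the burn, and its closing qualifier does not reconcile them. For any child enrolled more than 3 (or 6) months after the burn, the 3-month (or 6-month) post-burn comparison has no scheduled value.

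How many children this touches cannot be said, because the article gives no distribution of time from burn to baseline. If nearly all enrol within days of injury and post-procedure means the baseline visit, the practical effect is small. If scar-management attenders are numerous, it is not. The conclusion rests only on the stated schedule and the entry criteria.

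The missing 6-month pain and itch measurements are a matter for clarification, not a second contradiction. It should be corrected, but it does not threaten the feasibility aims.

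**What to change.** 1. In Data analysis, Patient-centred outcomes, state that group differences are examined at the scheduled times after baseline, and replace the post-procedure and post-burn wording accordingly.
2. Include days post-burn at baseline in the outcome models as a prespecified covariate, whether or not the groups are found to differ on it. Its functional form can be left to the analysis plan.
3. As a clarification, refer to Table 2 for the analysis times of each outcome. State that pain and itch (FLACC and numeric rating scale) have a 3-month follow-up comparison and no 6-month one, and that 6-month comparisons cover the outcomes marked at that time: distress, stress, satisfaction and health-related quality of life.

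The cost is a few sentences of wording and one model term (more if a curved form is chosen). No visit, measurement or participant is added, since days post-burn is already to be collected.
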